#### Statistical analysis

All the intervention evaluations will be performed on an intention-to-treat basis. Multiple imputations by chained equations will be used to account for missing values.

Patient characteristics will be summarized by comparison group and tested for differences using *t*-tests and chi-square tests. To assess the effectiveness of each initial antihypertensive regimen and protocol, we will estimate a mixed-effects generalized linear model for each outcome including indicators for treatment groups, baseline blood pressure, and imbalanced patient characteristics. Additionally, we will perform pre-specified subgroup analyses of outcomes by age, sex, education, smoking status, and tertiles of baseline blood pressure. Considering potential crossovers among treatments, we will also assess the heterogeneity of the treatment effect among per-protocol populations.

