#### Recruitment of patients

The patients at the intervention sites of the LIGHT trial are eligible if they have a measured baseline SBP ≥140 mmHg and are taking 0–1 class of antihypertensive medication. Key exclusion criteria include diabetes mellitus and intolerance to at least one of the four classes of antihypertensive medications (Table 1). The eligible patients in the LIGHT-ACD trial are categorized into 2 subpopulations. Patients with an SBP of 140–159 mmHg who are not taking any antihypertensive medication are categorized as Population 1, the remainder as Population 2.

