#### Randomization and blinding

Populations 1 and 2 are randomized to different antihypertensive regimens separately. Minimization randomization [26] is used to ensure the balancing of age, gender, and education level among different arms. The allocation is centrally performed and concealed within the CDSS. Neither doctors nor patients are blinded to treatment allocation. Population 1 individuals are randomized to receive one of the initial monotherapies of A (ACEI or ARB), C (CCB), or D (diuretics). If additional treatment is needed, they are further randomized to add either C or D, so patients initiated with A follow either A-AC-ACD or A-AD-ADC with C and D as the add-on medications, respectively. The randomization of drug regimen among patients initiated with C or D is similar to patients initiated with A. Population 2 individuals are randomized to receive one of the three initial dual therapies of AC, AD, or CD. Subsequently, D, C, or A are added to achieve blood pressure control, if necessary, respectively (Fig. 1).

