#### Outcomes

The primary outcome is the difference in the change in blood pressure from baseline to 9 months between different drug regimens of initial therapy. Secondary outcomes include the proportion of individuals with blood pressure controlled at 9 months; the proportion of individuals with SBP <160 mmHg and DBP <100 mmHg at 9 months; the proportion of individuals who received monotherapy (only in Population 1), dual therapy, triple therapy, and referral at 9 months; the proportion of individuals reported to have antihypertensive drug-related side-effects; and the proportion of individuals transferred to usual care for any reasons. The exploratory outcome is the change in blood pressure from baseline to 9 months of six protocols embedded in the CDSS (Table 2).

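### LIGHT-ACD adjusts for whichever baseline characteristics look imbalanced, a rule that almost never admits the minimisation factors; the result is conservative tests and some lost power

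*Protocol article*

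**What the plan says.** All references are to the LIGHT-ACD part of the protocol article.

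- **Statistical analysis, baseline tests:** "Patient characteristics will be summarized by comparison group and tested for differences using *t*-tests and chi-square tests". No significance level is given for these tests.
- **Statistical analysis, model:** the next sentence says "we will estimate a mixed-effects generalized linear model for each outcome", with the terms "including indicators for treatment groups, baseline blood pressure, and imbalanced patient characteristics". Baseline blood pressure is therefore always in the model. The other covariates are not named, and imbalance is not otherwise defined.
- **Randomization and blinding:** "Populations 1 and 2 are randomized to different antihypertensive regimens separately", and minimisation "is used to ensure the balancing of age, gender, and education level among different arms".
- **Outcomes:** "The primary outcome is the difference in the change in blood pressure from baseline to 9 months between different drug regimens of initial therapy". The model sentence covers every outcome, so it covers this one.

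The statistical analysis section names age, sex and education only as subgroup variables. It does not require them as covariates.

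**The concern.** Two features of the plan work against each other.

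First, under randomisation any baseline difference between arms is chance. A significance test of that difference does not show whether the variable predicts blood pressure change, and prognostic value is the reason to adjust.

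Second, minimisation keeps its factors balanced, so a rule that admits only imbalanced variables leaves out the variables that governed allocation. Balancing on prognostic factors makes the treatment difference less variable. A model without those factors does not register the gain: it leaves their variance in the residual and reports too large a standard error. The tests are then stricter than their nominal level and power is lost.

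The covariate set of the primary model is also unknown until the baseline data are tabulated by arm.

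**Working it through.** **Inputs from the LIGHT-ACD sample size section.** SD of SBP 10 mmHg; alpha 0.017 per comparison (Šidák for three); about 2100 completers, split 25%/75%; 80% power for 3.5 mmHg (Population 1) and 2 mmHg (Population 2).

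**Assumptions, not in the protocol.** Equal arms and two-sided tests; R² = 5%, 10% or 20% of outcome variance explained by age, gender and education together; baseline tests at 5%.

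**1. The plan's own power.** Per arm, 2100 × 0.25 / 3 = 175 and 2100 × 0.75 / 3 = 525. With z(0.017) = 2.387, SE = 10 × √(2/n), and power = Φ(difference/SE − 2.387):

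- Population 1: SE = 1.069; Φ(3.5/1.069 − 2.387) = 0.813; difference detectable at 80% = (2.387 + 0.842) × 1.069 = 3.45 mmHg.
- Population 2: SE = 0.617; Φ(2/0.617 − 2.387) = 0.803; detectable difference 1.99 mmHg.

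The stated power is reproduced, so these inputs are used below.

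**2. Does the rule admit the minimisation factors?** A simulation used 525 patients in three arms, minimised with a biased coin of 0.8 on age (3 levels), gender (2) and education (3), with 3000 runs per setting. The levels and the coin are assumptions. Age, gender and education were flagged at p < 0.05 in 0 of 3000 runs. Under simple randomisation each was flagged in about 5%.

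**3. Standard error and true size when they are left out.** The reported SE is too large by 1/√(1 − R²), and the true size is 2 × (1 − Φ(2.387/√(1 − R²))).

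| R² | SE ratio | True size, formula | Simulated, test-selected model | Simulated, factors always in |
|---|---|---|---|---|
| 5% | 1.026 | 0.014 | 0.014 | 0.016 |
| 10% | 1.054 | 0.012 | 0.012 | 0.016 |
| 20% | 1.118 | 0.008 | 0.007 | 0.016 |

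**4. Power in Population 1 at 0.35 SD (3.5/10).** From step 1, 3.5/1.069 = 3.274. With the factors omitted, power = Φ((3.274 − 2.387)/√(1 − R²)). With them included, power = Φ(3.274/√(1 − R²) − 2.387).

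| R² | Omitted, formula | Included, formula | Simulated, test-selected | Simulated, pre-specified | Simulated loss |
|---|---|---|---|---|---|
| 5% | 0.819 | 0.835 | 0.812 | 0.829 | about 2 points |
| 10% | 0.825 | 0.856 | 0.818 | 0.857 | about 4 points |
| 20% | 0.839 | 0.899 | 0.836 | 0.897 | about 6 points |

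**5. Chance entry of other variables.** For k independent characteristics tested at 5%, P(at least one flagged) = 1 − 0.95^k. This gives 23% for k = 5, 34% for k = 8 and 40% for k = 10. The simulation with five unrelated variables gave 24%.

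**The case against.** **The rule is partly inferred.** The protocol does not say that imbalanced means significant on a t-test or chi-square test, and a statistical analysis plan not shown here may define it. This stands as a caveat. But the two sentences are adjacent, and any definition based on observed balance has the same fault. The protocol states the rule itself, so this is more than an omitted detail.

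**The harm is modest.** This stands. In the simulations power under the test-selected model was still 0.81 to 0.84, above the planned 80%. If the three factors add little to baseline blood pressure, which is always in the model, the loss is negligible. A chance-selected covariate that is not prognostic barely moves the estimate.

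Some stronger readings that a reader might infer are not supported:

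- **Inflated type I error.** The calculation shows the opposite: size falls below 0.017.
- **Analyst discretion made worse by the open-label design.** On the natural reading the rule is mechanical and uses baseline data, not outcomes; open-label prescribing does not affect it.
- **t-tests cannot be used with three arms.** The sample size section plans three pairwise comparisons, and pairwise t-tests are possible.
- **An invalid Population 2 comparison.** The protocol says eligible untreated patients with SBP 140–159 mmHg "are categorized as Population 1, the remainder as Population 2", so Population 2 mixes untreated patients with patients already on one class. It is randomised separately, so the pooled comparison is valid without adjustment for treatment at entry.

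**Conclusion.** The concern holds as a poorly chosen covariate rule. As written, the LIGHT-ACD models would almost never include the factors used to allocate patients, and chance would decide which other characteristics enter.

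The effect is conservative. For R² of 5 to 10%, true size is about 0.014 to 0.012 against 0.017, the SE is overstated by about 2.6 to 5.4%, and Population 1 loses about 2 to 4 points of power. These sizes rest on the assumed R²; the 0 of 3000 result rests on the assumed minimisation settings. The 23 to 40% chance that at least one other variable enters assumes five to ten independent characteristics tested at 5%.

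The validity of the randomised comparisons is not in question. The change should be made because it recovers precision and fixes the primary model at almost no cost.

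**What to change.** In the LIGHT-ACD statistical analysis section, remove the adjustment for imbalanced characteristics and stop using baseline significance tests as a selection rule; the descriptive summary by arm can stay. For each population, pre-specify a model with randomised arm, the baseline value of the blood pressure measure analysed (SBP for the SBP analysis, DBP for the DBP analysis), age, gender and education, kept whatever the observed balance.

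Optionally, add treatment at entry as a pre-specified covariate in Population 2 to gain precision.

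Cost: wording only. Table 3 lists blood pressure, age, gender, education and current medications as already collected.

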## Discussion

The LIGHT trial is, to the best of our knowledge, the largest pragmatic randomized trial exploring the feasibility and effectiveness of a decision support tool to deliver high-quality care for hypertension in primary care. Moreover, by adopting a streamlined study design, we have nested a patient-level randomized trial (LIGHT-ACD trial) into this cluster-randomized trial using an algorithm-based CDSS tool.

Our studies have several potential strengths. First, we have developed a usable CDSS, which can easily be integrated into the routine clinical workflow and provides tailored antihypertensive recommendations at the point of care. These features are highly correlated with the effectiveness of CDSS for improving the process of care and patient outcomes [23, 29, 30]. As recommendations of CDSS are generated automatically by the built-in algorithm, which is developed based on current guidelines, this approach can assist primary care doctors, even those with less training, in making informed and evidence-based prescribing decisions.

Second, we have built a streamlined framework for a clinical trial that enabled us to compare the effectiveness of several guideline-based initial antihypertensive regimens. Earlier randomized clinical trials such as the ALLHAT [18] and ACCOMPLISH [31] trials provided a direct comparison among several monotherapies or dual therapies. These trials are not contemporary and did not include large Asian populations, so there remain gaps in knowledge. In contrast with these standalone trials, the conduct of the LIGHT-ACD trial is embedded into the existing framework of the LIGHT trial. We incorporate a series of stepped treatment protocols into the CDSS, whereby the random allocation of recommended medication can be performed automatically by following the algorithm-consistent order at each encounter where decision support is delivered [32]. While assessing the effectiveness of CDSS, the effectiveness of common initial antihypertensive monotherapies or dual therapies can be compared unobtrusively [31, 33–35].

Third, the pragmatic design of both trials enables us to demonstrate the real-world effectiveness of intervention/treatment with greater external validity [36, 37]. In contrast to trials with study-specific visits, the enrolment and follow-up of patients, and the collection of outcome data in our trial are incorporated into routine clinical practice. Furthermore, the exclusion criteria are kept to a minimum to enroll a diverse spectrum of the population. These considerations improve the efficiency of trials and enhance the generalizability of the study results [37].

Fourth, the two studies are further distinguished by the efforts to build a learning decision support tool. Although the algorithm of CDSS is kept consistent during the four stages of the trial, it has the potential to be adaptively updated after the results of the LIGHT-ACD trial are available. For the ultimate implementation of the CDSS, the tool could continuously generate new knowledge in terms of the effectiveness of treatment strategies from the ongoing delivery of care, whereby the CDSS could be iteratively tested and improved by shifting the randomization ratio of stepped antihypertensive protocols toward the more effective group [38].

Our study has some potential limitations. First, the outcomes are focused on surrogate outcomes and not clinical outcomes such as cardiovascular events. To examine the effect on clinical events, a much longer trial would be required. However, it is expected that improvements in blood pressure control over time would favorably affect clinical outcomes. Second, given the nature of the CDSS, which delivers its recommendation directly to doctors, blinding was not feasible. We minimized the potential bias by using objective measures as primary and secondary outcomes. Third, due to the limited timeframe of the study, an extended follow-up was not included following the intervention to measure the persistence of effects after the intervention ceases. Fourth, we did not include consideration of diet, in part because of issues of the validity of self-reporting. In this trial, we only collected information necessary for pharmacological hypertension management such as the blood pressure measurements, comorbidities, current medications, and prescriptions. However, the confounding effect of diet may have been minimized through site randomization.

In conclusion, both trials should be able to provide useful evidence regarding the effectiveness of this decision support tool on improving adherence to guidelines for hypertension management in primary care, and on the comparative effectiveness of different initial antihypertensive regimens for blood pressure reduction in the real-world setting.

### Trial status

Protocol version 4.4 commenced on December 28, 2020. As of May 2021, 94 sites (including 7,656 patients in LIGHT and 494 participants in the LIGHT-ACD trial) have been randomized in 4 stages. Site randomization of Stage 1 was on 21 August 2019, Stage 2 on 4 December 2019, Stage 3 on 1 March 2021, and Stage 4 on 14 April 2021. The implementation of the trial is affected by the outbreak of COVID-19, we have extended the enrolment and follow-up periods appropriately in each stage of the trial. Currently, all sites will complete follow-up by the middle of 2022.

## Data Availability

The datasets used and/or analyzed during the current study will be available from the corresponding author on reasonable request.
